# High-Definition Transcranial Direct Current Stimulation (HD-tDCS) Therapy in Amyotrophic Lateral Sclerosis: Study Protocol for a Multicenter Randomized Controlled Clinical Trial

**DOI:** 10.3390/jcm14196701

**Published:** 2025-09-23

**Keywords:** neuromuscular diseases, transcranial electrical stimulation, home-based treatment

## Abstract

**Background/Objectives:** Amyotrophic Lateral Sclerosis (ALS) is a progressive and fatal neurodegenerative disease characterized by motor neuron loss, muscle weakness, and respiratory dysfunction, often culminating in ventilatory failure. Evidence suggests that High-Definition Transcranial Direct Current Stimulation (HD-tDCS) may modulate motor cortical excitability and potentially influence motor and respiratory function in ALS. This study aims to evaluate the effects of home-based HD-tDCS applied over the primary diaphragmatic motor cortex on respiratory parameters and disease progression in individuals with ALS. **Methods:** This is a multicenter, randomized, controlled clinical trial. Eligible participants (aged 18–80, both sexes, diagnosed with ALS) will be randomized into an active HD-tDCS group (gTDCS) or a sham group (gSham). The intervention consists of 30 min daily HD-tDCS sessions (3 mA) applied for two weeks (5 days/week), using a 4 × 1 ring configuration targeting the diaphragmatic motor cortex. Sham stimulation includes an identical setup but only delivers ramp currents (30 s) with a minimal ongoing current (0.1 mA). **Results:** Pre-, intra-, and post-intervention evaluations will include measures of cortical excitability, cerebral and tissue perfusion, surface electromyography, respiratory and pulmonary function, fatigue, sleep quality, pain, motor performance, dyspnea, quality of life, and adverse effects. All procedures will be conducted at participants’ homes with appropriate safety monitoring. **Conclusions:** This study will investigate the effects of HD-tDCS on respiratory and motor function in ALS and explore the feasibility of a home-based neuromodulation intervention. The outcomes may provide insight into non-pharmacological strategies for respiratory management in ALS.

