### 1.1. Objectives

#### 1.1.1. Primary Objective

To evaluate the effects of HD-tDCS on respiratory function and neurophysiological responses associated with stimulation of the diaphragmatic primary motor cortex in individuals with ALS.

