#### 1.1.2. Secondary Objectives

▪To assess cortical excitability by measuring patterns of facilitation, inhibition, active and resting motor thresholds, central motor conduction time, cortical silent period, and Motor Evoked Potentials (MEPs) in individuals with ALS;▪To evaluate cortical tissue perfusion in the region of the diaphragmatic primary motor cortex in individuals with ALS through specific respiratory tests before and after the HD-tDCS intervention protocol;▪To assess respiratory muscle electrical activity in individuals with ALS before and after the HD-tDCS intervention protocol;▪To observe the effects of HD-tDCS on aspects such as respiratory muscle strength, nasal inspiratory and expiratory pressures, and peak cough flow through specific respiratory tests in individuals with ALS;▪To observe the effects of HD-tDCS on clinical and functional aspects using the Amyotrophic Lateral Sclerosis Functional Rating Scale—Revised (ALSFRS-R);▪To assess motor control and muscle performance using a protocol for evaluating peripheral muscle electrical activity;▪To assess fatigue, dyspnea, pain, sleep, quality of life, and cognition before and after the HD-tDCS intervention protocol;▪To identify adverse effects of HD-tDCS on the diaphragmatic motor cortex in individuals with ALS.

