### 2.2. Sample Recruitment, Randomization, and Blinding

Participants will be recruited by direct invitation to the Neuromuscular Disease Clinic of the University Hospital, where they have already been diagnosed and receive follow-up care from a multidisciplinary team. Only those who meet the eligibility criteria will be included in the study. After being invited to participate and given a clear explanation of all procedures involved in the research, including the possibility of being assigned to the control or experimental group, each individual will have one week to discuss the decision with their family. Following this period and after signing written consent, participants will be taken to the lab for baseline evaluation. Patients will receive interventions at home and will be evaluated at outpatient units and research labs. Being informed of the benefits of conducting tDCS therapy at home may enhance patient adherence to treatment by reducing transportation costs and associated risks.

The sample will consist of individuals with ALS who have signed the Informed Consent Form (ICF) (Supplementary Materials S1) authorizing their participation in the research and meet the study’s inclusion criteria. Participants will be randomized by an external researcher (using sealedenvelope.com) into two groups: the HD-tDCS group (gTDCS) and the sham group (gSham). Randomization will be carried out in a 1:1 ratio with permutation blocks of size unknown to the investigators. Each participant will have an equal probability of being assigned to either group. Evaluators, therapists, and participants will be blinded to the group allocations, as will the person responsible for statistical analysis.

The planned sample will seek a balanced distribution between the sexes whenever possible, recognizing the influence of the variations in the effects of transcranial stimulation due to the anatomy of the skull, cortical excitability, and neuroplasticity. The HD-tDCS device is configured to allow a preset stimulus model with specific timing and intensity codes, which cannot be identified during intervention. These codes, associated with each intervention group, will be programmed and provided by an external researcher to maintain blinding.

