### 2.4. Interventions

Participants in the gTDCS will receive anodal high-definition direct current stimulation at an intensity of 3 mA on the diaphragmatic motor cortex through electrodes fixed in a cap. The stimulation will begin with a 30 s ramp-up to reach the intended intensity, followed by a 30 min session, and ending with a 30 s ramp-down. This will be conducted daily for 2 weeks (10 days), excluding weekends, at the same time each day in the participant’s home. The anodal current was chosen for motor cortex stimulation due to its potential for functional modulation, without directly inducing action potentials or neuronal hyperexcitability [25]. The intervention will be administered by a trained research professional with experience in neuromodulation techniques.

In the gSham, individuals will undergo all steps of the intervention and assessment protocol, but stimulation will be set to reach an intensity of 0.1 mA after the initial 30 s ramp-up, with the 3 mA current only returning in the last 30 s, resulting in no significant intervention during the 30 min.

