### 2.7. Measurement of Outcomes

The outcome measures and tools used are listed in the following table according to the intended endpoint and in the order of the proposed objectives. In addition to these data, sociodemographic information, including gender, age, marital status, education, and employment, as well as lifestyle habits such as alcohol consumption, tobacco use, hours of sleep, and clinical information such as medication use, are included (Table 1).

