Although techniques such as neuronavigation and real-time functional neuroimaging allow for more precise stimulation, their absence does not preclude the clinical application of neuromodulation. Previous studies indicate that stimulation based on standardized anatomical coordinates—even without neuronavigation—can produce physiologically relevant effects, especially when the target is the primary motor cortex, whose location is relatively well defined. However, anatomical variability among individuals, both in cortical positioning and in the functional representation of the diaphragm, may influence individual responses to the intervention. This variability underscores the importance of complementary functional monitoring, such as the use of functional neuroimaging techniques (fNIRS, EEG) or physiological measurements (respiratory pressures, electromyography), to validate the response to the protocol. Moreover, if no statistically significant differences are observed between the gSham and gTDCS groups, the findings will still yield important insights regarding the feasibility, safety, and methodological challenges of implementing HD-tDCS in individuals with ALS. These results may guide future adjustments to stimulation parameters, participant stratification strategies, or the incorporation of additional biomarkers.

Therefore, the selection of a cortical target—particularly the diaphragmatic primary motor cortex—is supported by anatomical, functional, and clinical evidence. The strategy aims to modulate cortical respiratory drive, enhance sensorimotor integration, and provide compensatory support in the face of the progressive failure of lower motor neurons—a central mechanism in the pathophysiology of ALS.

In terms of dissemination, the results of the study will be shared through peer-reviewed publications, as well as presentations at national and international conferences, particularly those focused on ALS, neurostimulation, and respiratory therapies. Additionally, we plan to make the data publicly available in open-access repositories to ensure transparency and foster further research in this field.

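### Feasibility is announced as something the trial will explore and as a yield of a null result, but no objective or listed outcome measures it, and non-completers are listed for exclusion

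*Protocol article*

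**What the plan says.** The abstract's conclusions state that the study will "explore the feasibility of a home-based neuromodulation intervention". Section 4 (Discussion) says that, if no significant difference is found between the arms, "the findings will still yield important insights regarding the feasibility, safety, and methodological challenges of implementing HD-tDCS in individuals with ALS".

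The primary objective (section 1.1.1) is "To evaluate the effects of HD-tDCS on respiratory function and neurophysiological responses associated with stimulation of the diaphragmatic primary motor cortex". Of the eight secondary objectives in section 1.1.2, the closest to feasibility is the last: "To identify adverse effects of HD-tDCS on the diaphragmatic motor cortex in individuals with ALS". On outcomes, section 2.7 says: "The outcome measures and tools used are listed in the following table according to the intended endpoint". It adds that Table 1 follows the order of the objectives.

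On delivery, section 2.4 says: "The intervention will be administered by a trained research professional with experience in neuromodulation techniques". Section 2.2 suggests that treatment at home may improve adherence, but attaches no measure to this. Section 2.3 puts participants who withdraw, or who do not finish the intervention, in the list of exclusion criteria.

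On location, the abstract says "All procedures will be conducted at participants’ homes with appropriate safety monitoring", while section 2.2 says "Patients will receive interventions at home and will be evaluated at outpatient units and research labs".

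**The concern.** Feasibility is promised twice, but nothing in the objectives or the outcome list produces a feasibility result. The second promise matters more, because it applies when the efficacy comparison is null. In that case feasibility becomes part of what the trial offers, and it would rest on whatever happened to be recorded.

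The exclusion list makes this worse. Whether someone finishes the sessions is known only after randomisation. If those who do not finish are then treated as excluded, the sample loses the people who would show that the treatment was hard to deliver or tolerate. A feasibility statement based on the remainder would be favourable whatever had happened.

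Reasons for missed sessions and equipment faults are also difficult to reconstruct later if they are not logged on the day.

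**Working it through.** This is mainly a check of consistency between sections, followed by a short calculation to show scale.

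**1. Objectives.** One primary and eight secondary objectives are listed. They cover respiratory function, neurophysiology, perfusion, muscle activity, functional and patient-reported measures, and adverse effects. None covers recruitment, acceptance, adherence, session completion, retention or equipment performance.

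**2. Outcomes.** Table 1 has 16 rows: cortical excitability, cerebral perfusion, respiratory muscle activity, nasal pressures, cough peak flow, functionality, motor control, fatigue, fatigue/dyspnoea, pain, sleep, quality of life, cognition, adverse effects, lung function and vital signs. Rows that measure feasibility: 0 of 16. Safety, named in the same Discussion sentence as feasibility, has both an objective and a row. Feasibility has neither.

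**3. What a completion outcome would yield.** Inputs from the article: 20 participants at each of 3 centres (section 4) and 10 sessions each (section 2.4).
- Participants: 20 × 3 = 60, which agrees with the stated total.
- Planned sessions: 60 × 10 = 600.

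The article gives no expected completion rate, so 70% to 90% is assumed. Exact (Clopper-Pearson) 95% intervals over all 60 randomised:

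| Completers (assumed) | Proportion | 95% CI |
|---|---|---|
| 42/60 | 70% | 0.57 to 0.81 |
| 48/60 | 80% | 0.68 to 0.89 |
| 54/60 | 90% | 0.80 to 0.96 |

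The Wilson interval for 48/60 is nearly the same: centre 0.782, half-width 0.100, so 0.682 to 0.882.

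**4. What happens if non-completers are excluded.** The denominator becomes the completers, so the proportion is x/x = 100% for any x. When every unit is a success, the exact lower limit is 0.025^(1/x). For x = 48 this is 0.025^(1/48) = exp(−3.689/48) = 0.926. In the 80% scenario the reported figure would be 100% (95% CI 0.93 to 1.00), an interval that does not contain the 80% that occurred.

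**5. Location.** The abstract puts all procedures in the home. Section 2.2 puts evaluations in outpatient units and laboratories, and section 2.4 requires structural MRI at the first evaluation. The statements do not agree.

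**The case against.** Much can be said for the plan, and several stronger readings fail.

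- **Feasibility is not a formal aim.** The abstract's aim sentence concerns effects on respiratory parameters and disease progression. Feasibility appears only in its conclusions, as something to explore, with no hypothesis or threshold. This stands, and it limits the seriousness of the point. It does not explain how exploration would proceed without a measure.
- **The Discussion sentence is about HD-tDCS in ALS generally.** It does not mention home delivery. A reader might infer that home feasibility is the declared fallback conclusion, but the text does not say so.
- **The trial is not without relevant data.** Adverse effects are graded for intensity and relation to stimulation, side effects are monitored at each session, and a CONSORT flow diagram is planned. These give some tolerability and retention information. To say that nothing would be measured goes too far.
- **Table 1 is not exhaustive.** Maximal mouth pressures are measured under section 2.5.1 but have no row in the table. Absence from Table 1 therefore does not prove that sessions go unlogged, and a fuller protocol or case report form may hold such details. The remaining point is narrower: the article sets out its objectives and outcomes at length, makes a feasibility claim, and defines no measure for it.
- **Delivery by a research professional is compatible with home-based treatment.** A reader might infer that this rules out any feasibility conclusion. It does not, because the article never claims self-administered or caregiver-run treatment. It only limits the conclusion to professionally delivered sessions.
- **The location conflict is a separate wording error.** It does not show that feasibility goes unmeasured.

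**Conclusion.** The point holds in a limited form. The article says feasibility will be explored and will be informative after a null result, but none of its nine objectives (1 + 8) and none of its 16 outcome rows defines a feasibility measure. The exclusion wording, read literally, would make completion 100% by construction. Existing adverse-effect and flow data cover part of the question. They do not cover sessions received, reasons for missed sessions or set-up faults, and the article does not show that acceptance among eligible patients will be recorded.

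This rests on two readings: that the objectives are stated in full in the article, and that the non-completion criterion would be applied after randomisation, the only time it can be. The completion figures are assumptions used for scale. No figure in the article is shown to be wrong, and the efficacy comparison does not depend on this point. The exclusion wording may also affect that comparison, but that is a separate question. The change is worth making because it is cheap and determines whether a stated conclusion has data behind it.

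**What to change.** Add one feasibility objective and one Table 1 row containing:
- sessions delivered out of 10, and the proportion receiving all 10, over all randomised participants;
- reasons for missed or stopped sessions;
- device or electrode faults;
- the proportion of eligible patients who accept.

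Take non-completion out of the exclusion criteria in section 2.3, so that non-completers stay in the denominator. This concerns who is counted and leaves the rules for stopping treatment unchanged.

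In the abstract and Discussion, describe the result as feasibility of professionally delivered HD-tDCS at home. If the sponsor prefers not to add the measures, withdraw both feasibility statements.

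Separately, reconcile the abstract's sentence on location with section 2.2.

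The cost is a one-line log at each of up to 600 home sessions that staff already attend, a count of invitations and acceptances, and some rewording. The downside is a narrower feasibility claim.

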## 1. Introduction

Amyotrophic Lateral Sclerosis (ALS) is an acquired, degenerative, and disabling nervous system disease characterized by the loss of motor neurons in the cortex, brainstem, and spinal cord [1]. People with ALS experience muscle weakness that progresses to loss of mobility and functionality, swallowing difficulties, and respiratory muscle dysfunction, and frequently results in death due to ventilatory failure [2]. As such, ALS is one of the most disabling neuromuscular diseases, with rapid and essentially fatal progression. The most common global symptoms faced by people with ALS include sialorrhea, spasticity, muscle atrophy, balance deficits, cognitive impairment, ventilatory insufficiency, increased bronchial secretions, muscle cramps, insomnia, fatigue, and difficulties with communication, swallowing, and nutrition [3,4].

Fundamental aspects of disease progression relate to motor and respiratory function. Muscle weakness progresses from the early stages of the disease, being asymmetrical and variable between the upper and lower limbs, with low resistance to effort and consequently reduced functional performance, which negatively impacts quality of life [5]. Progressive loss of respiratory muscle strength is one of the main challenges for ALS patients. Although this loss plays a significant role in the natural history of the disease, it varies, occurring more rapidly in some individuals and more slowly in others [6].

The death of respiratory motor neurons in ALS leads to denervation and partial reinnervation of respiratory muscle fibers by adjacent motor axons. This collateral reinnervation gives rise to larger, more complex motor units that may partially preserve global respiratory function but compromise more complex motor activities, such as the coordination between breathing and swallowing and the control of sialorrhea [7].

In addition to peripheral failure, respiratory dysfunction in ALS is also manifested by a compensatory increase in the neural drive to breathe, as the central nervous system attempts to maintain ventilation. This neural overload occurs especially during sleep, when the automatic mechanisms of respiratory control are most demanded. Hypoventilation initially develops during the night, associated with sleep-disordered breathing such as sleep apnea and sleep fragmentation, and later extends into the daytime period. This imbalance is one of the main determinants of the need for ventilatory support and directly impacts patients’ quality of life and prognosis. Nocturnal hypoventilation is an early manifestation in ALS patients. Studies have shown that these patients present significantly worse spirometric values and blood gas parameters compared to those without nocturnal hypoventilation, suggesting that the loss of central ventilatory drive contributes to hypopnea and desaturation during sleep [8,9].

As the disease progresses, the continuous loss of respiratory motor neurons leads to muscle weakness and atrophy, resulting in progressive hypoventilation and the development of chronic respiratory failure, a factor directly related to reduced survival in these patients [7]. In patients with chronic obstructive pulmonary disease (COPD), ref. [10] demonstrated basal hyperexcitability in brain regions involved in compensating for respiratory loads, such as the motor and premotor cortices. Nguyen et al. [11] corroborated these findings, highlighting the association between cortical activity related to breathing and the increased perception of respiratory effort during ventilatory loads.

Cortical centers can directly influence spinal motoneurons, allowing indirect cortical control of respiratory muscle activity through the brainstem respiratory center [12,13,14,15,16]. The study by Azabou et al. [15] reported that transcranial direct current stimulation (tDCS) applied to the primary motor cortex was able to modulate the excitability of respiratory neural pathways, showing that anodal or cathodal stimulation in healthy individuals resulted in a reduction in the excitability of diaphragmatic corticospinal pathways. These findings support the potential for neuromodulatory interventions targeting central respiratory control.

In terms of survival, the lack of curative treatments or those that significantly alter the clinical course and progression of ALS has led to the search for new treatment alternatives, proposed in recent years. Over the last two decades, new therapeutic hypotheses have emerged, based on case studies on the application of transcranial direct current stimulation (tDCS). Specifically, different forms of modulation based on non-invasive brain stimulation techniques have been tested and evaluated as non-pharmacological methods for treating various neurological conditions.

tDCS is a brain modulation technique with a strong physiological basis and significant practical acceptance in the treatment of various neurological and musculoskeletal disorders. Studies point to interesting possibilities for using tDCS in treating motor and sensory dysfunctions and learning disorders, making it a potential adjunct to conventional treatments [12,13]. Stimulation can last minutes or even hours after the end of the session. Thus, it emerges as a potential tool for treating motor neuron diseases and degenerative neurological syndromes. Given its ease of application, minimal adverse effects, and relatively low cost, tDCS is clearly a feasible option for routine use in public and supplementary healthcare systems [17,18].

Although widely used, conventional tDCS has evolved into a more advanced form known as high-definition tDCS (HD-tDCS) [19]. This modality features smaller electrodes and a configuration involving a central electrode, with either anodic or cathodic current, surrounded by two or more electrodes with opposite polarity [20,21,22,23]. This configuration helps confine neuromodulation effects to the radius of the four electrodes and increases the focal effect, producing better results in the different areas of the stimulated motor cortex, including the diaphragmatic cortex, to investigate, for instance, changes in muscle strength and perceived exertion [23].

HD-tDCS has been widely investigated as a safe and non-invasive neuromodulation tool [21]. Unlike other forms of electrical stimulation, HD-tDCS does not directly generate action potentials but modulates cortical excitability, making the stimulated region more susceptible to responding to subsequent stimuli [24]. This modulation occurs in a complex manner, depending on the function and basal state of the local neural network, which involves interactions between excitatory and inhibitory neurons [25]. Evidence suggests that anodal tDCS, unlike cathodal tDCS, can induce beneficial functional effects without accelerating the progression of Amyotrophic Lateral Sclerosis (ALS) [26,27]. More recent studies indicate that anodal current applied to the motor cortex, combined with cathodal current to the spinal cord (conventional tDCS), may reduce disease progression [28,29]. Additionally, isolated cathodal tDCS has not demonstrated measurable effects on muscle strength or disease progression [30,31,32].

The study by Benussi et al. [29], using computational modeling of current flow and multichannel tDCS application—consisting of anodal stimulation of the right and left primary motor cortex with the cathodal electrode at the spinal region (C6)—aimed to achieve a synergistic effect from stimulating both structures. In a sample of thirty patients, significant improvements/stabilizations were observed in clinical scores of peripheral muscle strength, quality of life, and caregiver burden after 2 weeks of treatment. The protocol involved applying tDCS for 20 min/day at an intensity of 2 mA. Interestingly, these effects persisted for 6 months after the treatment ended, with clinical parameters and neurophysiological assessment through Transcranial Magnetic Stimulation (TMS) monitoring progress. Additionally, this study reported slower disease progression, expressed by a decline in the Revised Amyotrophic Lateral Sclerosis Functional Rating Scale (ALSFRS-R) score of less than 2 points over 6 months, characterizing the real tDCS and sham/control groups.

While there are studies suggesting neuromodulation effects through tDCS intervention in the ALS population, the effects of this therapy on the respiratory system remain unclear, creating a gap in the literature. Thus, the hypothesis of the present research is that HD-tDCS may stimulate motor areas related to respiratory muscles and produce significant effects on pulmonary function and stabilization of disease progression in individuals with ALS, with an initial focus on neurophysiological and respiratory outcomes.

